### Ethical considerations

The study protocol was approved by the human research ethics committees of the Department of Health and Ageing (Australian Government), Department of Human Services (Australian Government), Australian Institute of Health and Welfare (Australian Government), SA Department of Health (South Australian Government), Queensland Department of Health (Queensland Government), Department of Health Victoria (Victorian Government), and the Aboriginal Health Research Ethics Committee (Aboriginal Health Council of South Australia).

## Discussion

The DCP is designed to facilitate a robust yet pragmatic comparison of different, evidence-based models of care in order to evaluate how care can be improved for people with diabetes, and to determine the level of change that would be required to achieve this in the Australian context. Intervention 1 tests the extent to which current reforms (such as e-Health and clinical training initiatives) will improve care for people with diabetes. Intervention 2 tests the impact of altering primary care funding to create a ‘health care home,’ in which patients voluntarily register with a practice and are cared for by a multidisciplinary team coordinated by a care facilitator. Implementing the ‘health care home’ model of care (Intervention 2) at scale would involve substantial changes to the health system, and the DCP will therefore evaluate the incremental benefit of this intervention to ascertain if nationwide implementation is worthwhile.

A number of steps have been taken to ensure that this evaluation is rigorous and objective, and to increase the validity of the project’s final recommendations, including: introducing as much randomisation as is possible for this type of complex health reform; choosing populations to be representative of the Australian general practice landscape; and ensuring that the size of the trial will allow for testing of a range of different hypotheses (for example, whether the interventions work better in small or large practices and in urban or non-urban areas, and whether they affect people with more complicated diabetes and people with less complicated diabetes in different ways).

Two potential drawbacks of the trial design are that Medicare Locals/Divisions of General Practice only support one of the two interventions, and that patients are enrolled after practices have been randomised. It was necessary to retain both of these design features in order to make the trial workable. Firstly, requiring practices to support both interventions would have placed impossible demands on general practitioners, allied health professionals and Medicare Locals/Divisions of General Practice. The DCP’s approach means that Medicare Locals/Divisions of General Practice need only train practices in, and provide support for, one of the interventions, and any bias between Medicare Locals/Divisions of General Practice will be detected and corrected for by the DCP’s evaluation team. Secondly, postponing randomisation until patient enrolment was complete would have added a delay of six months (following initial sign up) for patients starting in the trial, and would have required control practices to be trained in the intervention in order for patients to give informed consent, thus confounding results.

The overall design of the trial is driven by the need to find practical and workable solutions to improving diabetes management in Australia that are informed by front-line experience. The trial has been developed through consultation with clinicians and patients during the design phase, and the project receives regular input from the national Diabetes Advisory Group, which comprises seventeen leaders of professional bodies representing various clinicians and people with diabetes. The consortium that is delivering the project consists of over twenty organisations (including Medicare Locals/Divisions of General Practice, state-based primary care organisations, state health departments and universities), and the project runs quarterly feedback forums with participating clinicians and patients.

The increasing global prevalence of diabetes, and the accompanying rise in complications and associated excess morbidity and mortality, suggest that the current approach to caring for people with diabetes can be improved. As the largest randomised controlled trial on the management of diabetes in Australia, the DCP has an opportunity to compare new, evidence-based approaches to diabetes management and to identify a model of care that improves health outcomes and patient and practitioner experiences, is scalable nationally and is economically sustainable. The outcomes of the study will have important implications not only for diabetes management, but also for the management of other chronic diseases, both in Australia and overseas.

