### Recruitment

Seven Medicare Locals/Divisions of General Practice (independent entities that are responsible for coordinating local primary health care services) [19] across the states of Queensland (n = 4), South Australia (n = 2), and Victoria (n = 1), Australia, are taking part in the trial. Prior to the commencement of the trial, each Medicare Local/Division of General Practice distributes study information sheets to all general practices (clusters) within their network and seeks expressions of interest to participate in the trial. Practices that express an interest in participating in the trial are enrolled in the project and randomly assigned to one of three treatment groups: control group, Intervention 1 or Intervention 2 (Figure 1). It is expected that fifty general practices will be enrolled in each group. Each enrolled practice is required to undergo training to familiarise themselves with the assigned intervention and study procedures. Medicare Locals/Divisions of General Practice that are assigned to Intervention 2 are supported by a ‘trial delivery and integration team’ to recruit and train care facilitators.

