### Randomisation

In four of the Medicare Locals/Divisions of General Practice, enrolled general practices are randomly allocated to the control group or Intervention 1 at a ratio of 1:2. In the other three Medicare Locals/Divisions of General Practice, practices are randomly assigned to the control group or Intervention 2 at a ratio of 1:2. A single type of intervention is tested in each Medicare Local/Division of General Practice as a result of two practical constraints: (1) care facilitators included in Intervention 2 are required to work with four or five practices within a single geographic area in order to work effectively; and (2) Medicare Locals/Divisions of General Practice would find it difficult to enrol and support practices using two different interventions, given that Intervention 1 and Intervention 2 comprise multiple components. Randomisation is applied after recruiting each group of three practices in a combined Medicare Local/Division of General Practice and Region stratum, where Region refers to urban or rural area. This helps to mitigate the potential bias created by testing only one intervention in each Medicare Local/Division of General Practice. Randomisation is applied separately for urban and rural practices within each Medicare Local/Division of General Practice because it is expected that service use and availability will differ by region. To approximate equality of sample sizes in each group, block randomisation is used with computer-generated, randomly permuted blocks of three. A researcher who is not involved in the implementation of the project and is blinded to the identity of the practices performs this task.

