### Interventions

Each general practice (cluster) is randomly assigned to one of the three treatment arms. Participants in the control group are assigned ‘usual care’, meaning that practices will continue to provide care as usual.

Practices assigned to Intervention 1 experience two changes: access to an online chronic disease management network (cdmNet) and access to training and capability building. The cdmNet decision support service is instrumental in generating, updating and reviewing multidisciplinary care plans; facilitating communication between team members; sharing patient information; engaging patients in their care; and facilitating service payments. The care plans generated by cdmNet in Intervention 1 are pre-populated with the minimum care requirements for the general diabetes population, as informed by best practice guidelines and recommended treatments for any recognised comorbidities. CdmNet also generates population-level clinical status reports that allow GPs to proactively manage their population of people with diabetes enrolled in the trial. The training and capability building has three main functions: to assist practices in implementing the new model of care and cdmNet; to provide regular access to endocrinologists/diabetologists; and to provide a forum where practices can find out about new developments in diabetes care and share their experiences with other trial participants.

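### Intervention 2 v Intervention 1 is an indirect, non-randomised comparison, but the article describes three-way randomisation, claims power for any two arms and promises that any between-area bias will be corrected

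*Protocol article*

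**What the plan says.** The protocol article describes the allocation in two ways.

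- **Three-way.** Recruitment says that practices are "randomly assigned to one of three treatment groups: control group, Intervention 1 or Intervention 2". Interventions says: "Each general practice (cluster) is randomly assigned to one of the three treatment arms". The Methods/Design part of the Abstract says the same in substance.
- **Two-way within area.** Randomisation says that in four Medicare Locals "practices are randomly allocated to the control group or Intervention 1 at a ratio of 1:2", and that in the other three "practices are randomly assigned to the control group or Intervention 2 at a ratio of 1:2". It adds: "A single type of intervention is tested in each Medicare Local/Division of General Practice as a result of two practical constraints". Recruitment refers to Medicare Locals assigned to Intervention 2 but gives no random method for that assignment.

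Randomisation says that blocking within area and region helps to mitigate the resulting bias. The Discussion lists the feature as a potential drawback, then states that "any bias between Medicare Locals/Divisions of General Practice will be detected and corrected for by the" evaluation team.

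Two further statements depend on the comparison of the interventions with each other. Primary outcome and Sample size calculation claim power for 0.25 HbA1c percentage points between any two arms. The Discussion says that "the DCP will therefore evaluate the incremental benefit of this intervention to ascertain if nationwide implementation is worthwhile", where the intervention meant is Intervention 2.

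**The concern.** Under the scheme in the Randomisation section, type of intervention coincides with a set of areas: four for Intervention 1, three for Intervention 2. No practice had a chance of receiving either intervention, so randomisation does not protect the comparison between them. Blocking within area balances each intervention against its own controls, not against the other intervention.

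The national policy question raised in the Discussion is what Intervention 2 adds. If that contrast is reported as one of three randomised pairwise comparisons, with power as for 50 v 50 practices and with between-area bias said to be corrected, readers will give it more weight than the design supports.

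**Working it through.** **1. Allocation probabilities (Randomisation).**

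| Areas | Control | Intervention 1 | Intervention 2 |
|---|---|---|---|
| Set A (four) | 1/3 | 2/3 | 0 |
| Set B (three) | 1/3 | 0 | 2/3 |

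No row has a positive probability for both interventions, so the three-way descriptions cannot be literally true.

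**2. What can and cannot be corrected.** Let a_A and a_B be the mean HbA1c change under usual care in the two sets, and e1 and e2 the intervention effects, with the set as suffix.

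- Direct comparison: (a_B + e2_B) − (a_A + e1_A) = (a_B − a_A) + (e2_B − e1_A).
- Comparison anchored on own-area controls: e2_B − e1_A. The usual-care difference has gone.
- Incremental effect within set B: e2_B − e1_B.
- Bias left after anchoring: (e2_B − e1_A) − (e2_B − e1_B) = e1_B − e1_A.

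Intervention 1 is never given in set B, so e1_B is not observed and the remaining term can be neither tested nor removed. The same holds for e2_A if set A is the target.

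**3. The plan's own figure.** Inputs from Sample size calculation: difference 0.25, SD 1.4, two-sided alpha 0.025, power 80%, design effect 3.45, attrition 20%, 50 practices and 1,250 patients per arm. The usual formula gives 2 × 1.4² × (2.241 + 0.842)² / 0.25² = 597 per arm. Then 597 × 3.45 / 0.8 = 2,575, not 1,250. The stated figure is not reproduced. That is a separate matter; the ratios below do not depend on SD, ICC or design effect.

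**4. Variance of each contrast.** Fifty practices per arm with 1:2 allocation imply 25 control practices beside each group of 50 intervention practices. In units of the variance of one practice mean:

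- 50 v 50, as the power statement assumes: 1/50 + 1/50 = 0.04.
- Each intervention v own-area controls, 50 v 25: 1/50 + 1/25 = 0.06, a ratio of 1.5.
- Intervention 2 v 1, anchored: 2 × (1/50 + 1/25) = 0.12, a ratio of 3.

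**5. Power, granting the claimed 80% for 50 v 50.** The implied standard error is 0.25 / (2.241 + 0.842) = 0.0811.

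| Contrast | SE | Power at 0.25 | Detectable at 80% |
|---|---|---|---|
| 50 v 50 | 0.0811 | 80% | 0.25 |
| Own-area control, 50 v 25 | 0.0811 × √1.5 = 0.0993 | about 61% | 0.25 × √1.5 = 0.31 |
| Intervention 2 v 1, anchored | 0.0811 × √3 = 0.1405 | about 32% | 0.25 × √3 = 0.43 |

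For the last row, 0.25 / 0.1405 = 1.780, and Φ(1.780 − 2.241) = 0.32.

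**6. Effect variation between areas (assumption; the documents give no figure).** If true effects vary between areas with SD τ, the contrast carries extra uncertainty of τ × √(1/4 + 1/3) = 0.76τ. For τ from 0.05 to 0.25 points this is 0.04 to 0.19 points, beyond the sampling error in step 5.

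**The case against.** The strongest reply is that nothing is hidden. Randomisation sets out the scheme with its practical reasons, and the Discussion lists it as a drawback. This stands: the fault is inconsistent description and over-assurance, not concealment. It is still a fault, because three sections state an allocation that did not apply.

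Secondly, the leading aims compare each intervention with usual care, and those contrasts are randomised within area. An alpha of 0.025 fits two comparisons (0.05/2), not three (0.05/3 = 0.0167). This stands too. A reader might infer that the whole trial lacks randomised evidence; it does not. But the power statement covers any two arms, and the Discussion relies on the incremental benefit of Intervention 2.

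Thirdly, Main analysis already adjusts for Medicare Local. Fitted as a fixed effect on follow-up or change, this yields the anchored contrast. In a repeated-measures model tested through time by group, an area main effect alone would remove differences in level but not in trend. The article does not say which is meant, and leaving that to an analysis plan is normal. It is no finding, but it shows why the contrast needs defining.

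Fourthly, how much each intervention's effect varies across its own areas can be estimated, which gives a rough gauge of responsiveness. With four and three areas it is imprecise, and it does not reveal a systematic difference between the two sets.

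Two stronger readings should be resisted. A reader might infer that Intervention 2 v 1 is known to be biased by a material amount; the documents give no size for any area difference, so a figure could only be assumed. A reader might also argue that seven areas split 4:3 cannot yield significance at 0.025, since the smallest permutation p-value is 1/35 = 0.029. No such test is planned, and practices, not areas, are the randomised unit.

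**Conclusion.** The point holds as one of description, assurance and stated power. Intervention 2 v 1 is not randomised under the article's own scheme. Differences in level or trend between areas can be removed through concurrent controls, but a systematic difference in treatment response between the four and the three areas cannot be told apart from intervention type. The assurance fails only in covering every bias.

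The size that can be stated is a threefold variance: about 32% power where 80% is claimed, and a detectable difference of about 0.43 rather than 0.25 points. This assumes 25 control practices in each set of areas, 1:2 allocation achieved in each area, equal practice sizes and variances, and 80% power granted for 50 v 50. It makes no allowance for effect variation between areas.

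**What to change.** - In the Abstract, Recruitment and Interventions, describe two parallel two-arm cluster randomisations, consistent with the Randomisation section.
- Keep each intervention v its own-area controls as the confirmatory contrasts.
- Estimate Intervention 2 v 1 as (Intervention 2 − own-area controls) minus (Intervention 1 − own-area controls), with areas allowed to differ in change over time. Label it indirect and dependent on no area-by-treatment effect modification.
- Replace the Discussion's assurance with a statement that differences in level and trend will be adjusted for, and that a difference in response between the two sets of areas cannot be separated from intervention type.
- Limit the power claim for any two arms and give this contrast its own figure, about 32% or 0.43 points on the plan's premise.
- Qualify the incremental-benefit conclusion to match.

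No change to allocation or conduct is needed. The cost is wording, one defined contrast and a restated power figure. The price is a weaker Intervention 2 v 1 claim and a less favourable stated power.
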